**Modified ODI**

|                |                                                                              |                          |
|----------------|------------------------------------------------------------------------------|--------------------------|
| Pain intensity | I have no pain now.                                                          |  |
|                | The pain is very mild now.                                                   |  |
|                | The pain is moderate now.                                                    |  |
|                | The pain is fairly severe now.                                               |  |
|                | The pain is very severe now.                                                 |  |
|                | The pain is the worst imaginable now.                                        |  |
| Personal care  | I can look after myself normally without causing extra pain.                 |  |
|                | I can look after myself normally, but it causes extra pain.                  |  |
|                | It is painful to look after myself, and I am slow and careful.               |  |
|                | I need some help but can manage most of my personal care.                    |  |
|                | I need help every day in most aspects of self-care.                          |  |
|                | I cannot dress, wash, or stand without help.                                 |  |
| Lifting        | I can lift heavy weights without extra pain.                                 |  |
|                | I can lift heavy weights, but it gives extra pain.                           |  |
|                | Pain prevents me from lifting heavy weights off the floor.                   |  |
|                | Pain prevents me from lifting heavy weights, but I can manage light weights. |  |
|                | I can lift only very light weights.                                          |  |
|                | I cannot lift or carry anything.                                             |  |
| Walking        | Pain does not prevent me from walking any distance.                          |  |
|                | Pain prevents me from walking more than 1 mile.                              |  |
|                | Pain prevents me from walking more than $\frac{1}{4}$ mile.                  |  |
|                | Pain prevents me from walking more than 100 yards.                           |  |
|                | I can walk only with crutches or a stick.                                    |  |
|                | I am in bed most of the time and must crawl to the toilet.                   |  |
| Sitting        | I can sit in any chair if I like.                                            |  |
|                | I can sit in my favorite chair if I like.                                    |  |

**The National Key Research and Development Program of China, No. 2021YFC1712802**

|               |                                                                                                                                                    |                          |
|---------------|----------------------------------------------------------------------------------------------------------------------------------------------------|--------------------------|
|               | Pain prevents me from sitting for more than 1 hour.                                                                                                |  |
|               | Pain prevents me from sitting for more than 30 minutes.                                                                                            |  |
|               | Pain prevents me from sitting for more than 10 minutes.                                                                                            |  |
|               | Pain prevents me from sitting at all.                                                                                                              |  |
| Standing      | I can stand if I want without extra pain.                                                                                                          |  |
|               | I can stand as long as I want but it gives me extra pain.                                                                                          |  |
|               | Pain prevents me from standing for more than 1 hour.                                                                                               |  |
|               | Pain prevents me from standing for more than 30 minutes.                                                                                           |  |
|               | Pain prevents me from standing for more than 10 minutes.                                                                                           |  |
|               | Pain prevents me from standing at all.                                                                                                             |  |
| Sleeping      | My sleep is never disturbed by pain.                                                                                                               |  |
|               | My sleep is occasionally disturbed by pain.                                                                                                        |  |
|               | Because of pain, I have less than 6 hours of sleep.                                                                                                |  |
|               | Because of pain, I have less than 4 hours of sleep.                                                                                                |  |
|               | Because of pain, I have less than 2 hours of sleep.                                                                                                |  |
|               | Pain prevents me from sleeping at all.                                                                                                             |  |
| Social life   | My social life is normal and gives me no extra pain.                                                                                               |  |
|               | My social life is normal but increases my pain.                                                                                                    |  |
|               | Pain has no significant effect on my social life apart from limiting more energetic activities.                                                    |  |
|               | Pain has restricted my social life, and I do not go out as often.                                                                                  |  |
|               | Pain has restricted my social life to my home.                                                                                                     |  |
|               | I have no social life because of pain.                                                                                                             |  |
| Traveling     | I can travel anywhere without pain.                                                                                                                |  |
|               | I can travel anywhere but it gives extra pain.                                                                                                     |  |
|               | Pain is bad but I can manage journeys over 2 hours.                                                                                                |  |
|               | Pain restricts me to journeys of less than 1 hour.                                                                                                 |  |
|               | Pain restricts me to short necessary journeys under 30 minutes.                                                                                    |  |
|               | Pain prevents me from traveling except to receive treatment.                                                                                       |  |
| Housework/job | Normal housework/job activities do not cause any pain.                                                                                             |  |
|               | Normal housework/job activities cause pain, but I can still manage to perform them.                                                                |  |
|               | I can perform most housework/job activities, but pain prevents me from doing physically demanding tasks (e.g., lifting, moving objects, cleaning). |  |
|               | Due to pain, I can only perform light physical tasks.                                                                                              |  |
|               | Due to pain, I am unable to perform even light physical tasks.                                                                                     |  |
|               | Due to pain, I cannot perform any job or housework at all.                                                                                         |  |

**(2) VAS**

The VAS is used to assess the intensity of the patient's leg and low back pain. Specifically, a 10-cm horizontal line is presented, with the left endpoint labeled “No pain (0)” and the right endpoint labeled

“Worst pain imaginable (10).” The patient is instructed to mark a vertical line (“/”) on the scale according to their perceived pain intensity. The physician then measures the distance (in centimeters) from the left endpoint to the patient's mark, with a longer distance indicating greater pain severity.

No pain (0)

Worst pain imaginable (10)

### (3) SF-12

The SF-12 assesses the quality of life through physical and mental dimensions, with scores typically ranging from 0 to 100. Higher scores indicate a better quality of life.

#### SF-12

|                                                                                                                                                                                                           |                                           |                                           |                                               |                                           |                          |                          |
|-----------------------------------------------------------------------------------------------------------------------------------------------------------------------------------------------------------|-------------------------------------------|-------------------------------------------|-----------------------------------------------|-------------------------------------------|--------------------------|--------------------------|
| In general, would you say your health is:                                                                                                                                                          |                                           |                                           |                                               |                                           |                          |                          |
|  Excellent                                                                                                                                                                        |  Very good        |  Good             |  Fair                 |  Poor             |                          |                          |
| The following questions are about activities you might do during a typical day. Does your health now limit you in these activities? If so, how much?                                               |                                           |                                           |                                               |                                           |                          |                          |
|                                                                                                                                                                                                           | Yes, limited a lot                        | Yes, limited a little                     | No, not limited at all                        |                                           |                          |                          |
| Moderate activities such as moving a table, pushing a vacuum cleaner, bowling, or playing golf.                                                                                                           |                   |                   |                       |                                           |                          |                          |
| Climbing several flights of stairs.                                                                                                                                                                       |                   |                   |                       |                                           |                          |                          |
| During the past 4 weeks, have you had any of the following problems with your work or other regular daily activities as a result of your physical health?                                          |                                           |                                           |                                               |                                           |                          |                          |
| Accomplished less than you would like.                                                                                                                                                                    |  Yes              |  No               |                                               |                                           |                          |                          |
| Were limited in the kind of work or other activities.                                                                                                                                                     |  Yes              |  No               |                                               |                                           |                          |                          |
| During the past 4 weeks, have you had any of the following problems with your work or other regular daily activities as a result of any emotional problems (such as feeling depressed or anxious)? |                                           |                                           |                                               |                                           |                          |                          |
| Accomplished less than you would like.                                                                                                                                                                    |  Yes              |  No               |                                               |                                           |                          |                          |
| Did work or activities less carefully than usual.                                                                                                                                                         |  Yes              |  No               |                                               |                                           |                          |                          |
| During the past 4 weeks, how much did pain interfere with your normal work (including work outside the home and housework)?                                                                        |                                           |                                           |                                               |                                           |                          |                          |
|  Not at all                                                                                                                                                                       |  A little bit     |  Moderately       |  Quite a lot          |  Extremely        |                          |                          |
| These questions are about how you have been feeling during the past 4 weeks. For each question, please give the one answer that comes closest to the way you have been feeling.                    |                                           |                                           |                                               |                                           |                          |                          |
| How much of the time during the past 4 weeks...                                                                                                                                                    |                                           |                                           |                                               |                                           |                          |                          |
|                                                                                                                                                                                                           | All the time                              | Most of the time                          | A good bit of the time                        | Some of the time                          | A little of the time     | None of the time         |
| Have you felt calm & peaceful?                                                                                                                                                                            |                   |                   |                       |                   |  |  |
| Did you have a lot of energy?                                                                                                                                                                             |                   |                   |                       |                   |  |  |
| Have you felt downhearted and blue?                                                                                                                                                                       |                   |                   |                       |                   |  |  |
| During the past 4 weeks, how much of the time has your physical health or emotional problems interfered with your social activities (like visiting friends, relatives, etc.)?                      |                                           |                                           |                                               |                                           |                          |                          |
|  All of the time                                                                                                                                                                  |  Most of the time |  Some of the time |  A little of the time |  None of the time |                          |                          |

## 6.2. Safety assessment

Blood routine tests and liver and kidney function tests were conducted before randomization and at 2 weeks after randomization. In addition, detailed records of each patient's gastrointestinal discomfort, skin allergies, and other AEs were collected at 2 weeks after randomization to assess safety.

## 6.3. Disc resorption assessment

At the 26-week post-randomization follow-up, a repeat MRI will be performed. The change in the sagittal area of the disc herniation from baseline to 26 weeks will be measured, with a reduction of  $\geq 40\%$  defined as the occurrence of disc resorption. The disc resorption rates will be calculated.

The maximum area of each disc herniation was measured on sagittal T2-weighted MRI sequences using Image J software (National Institutes of Health, Bethesda, MD, USA), with tracings made from the posterior edge of adjacent vertebrae in accordance with the measurement standards and definitions established by the North American Spine Society (NASS), the American Society of Spine Radiology (ASSR), and the American Society of Neuroradiology (ASNR) task force. All measurements were independently performed by two spine surgeons with extensive experience, and the average of their measurements was taken as the final result. The reliability assessment demonstrated good to excellent reproducibility.

The following table summarizes the data collection schedule and key assessment time points:

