#### **4.4. Drop-out criteria**

Participants who discontinue the study for any reason will be considered dropouts. Voluntary withdrawal will be permitted due to personal reasons, health concerns, or loss of confidence in the study protocol. Investigators will retain the right to withdraw participants for protocol violations, poor compliance, or deteriorating health status that makes continued participation inadvisable. For all dropouts, investigators will perform final safety and efficacy assessments whenever possible and document withdrawal reasons. All data from withdrawn participants will be included in the final intention-to-treat (ITT) analysis to maintain data integrity.

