#### **4.5. Discontinuation criteria**

Participants will be discontinued from the study under any of the following circumstances:

- (1) Adverse event (AE): Discontinuation will be required if a participant experiences:

- 1) A severe allergic reaction (e.g., anaphylaxis, angioedema) deemed related to the study intervention.
- 2) Any other drug-related AE that, in the investigator's judgment, poses a significant health risk or precludes further participation.

(2) Pregnancy: Confirmation of pregnancy during the study period will mandate immediate discontinuation.

(3) Participant Decision: Participants will be able to voluntarily withdraw from the study at any time, for any reason, without prejudice to their future medical care.

(4) Investigator-Initiated Discontinuation: The investigator will be able to discontinue a participant for safety reasons, protocol violations, or administrative necessities.

Procedures Following Discontinuation:

- (1) Upon discontinuation, the investigator will document the primary reason for withdrawal.
- (2) A final safety and efficacy assessment will be performed whenever feasible.
- (3) All discontinued participants will be followed as per protocol, with safety monitoring continuing until any unresolved AEs are resolved or stabilized.

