**Study schedule**

| Phase                           | Study visit | Treatment period |         |         | Follow-up period |         |         |
|---------------------------------|-------------|------------------|---------|---------|------------------|---------|---------|
| Visit                           | Enrollment  | Visit 1          | Visit 2 | Visit 3 | Visit 4          | Visit 5 | Visit 6 |
| Timing                          | Day 0       | Day 3            | Week 1  | Week 2  | Week 6           | Week 14 | Week 26 |
| Baseline data            |             |                  |         |         |                  |         |         |
| Inclusion criteria confirmation | √           |                  |         |         |                  |         |         |
| Exclusion criteria confirmation | √           |                  |         |         |                  |         |         |
| Informed consent obtained       | √           |                  |         |         |                  |         |         |
| Demographic data collected      | √           |                  |         |         |                  |         |         |
| Efficacy assessments     |             |                  |         |         |                  |         |         |
| ODI                             | √           | √                | √       | √       | √                | √       | √       |
| Leg pain VAS                    | √           | √                | √       | √       | √                | √       | √       |
| Low back pain VAS               | √           | √                | √       | √       | √                | √       | √       |
| SF-12                           | √           | √                | √       | √       | √                | √       | √       |
| Safety monitoring        |             |                  |         |         |                  |         |         |
| Complete blood count            | √           |                  |         | √       |                  |         |         |
| Liver function tests            | √           |                  |         | √       |                  |         |         |
| Renal function tests            | √           |                  |         | √       |                  |         |         |

|                          |   |   |   |   |  |  |   |
|--------------------------|---|---|---|---|--|--|---|
| Adverse events recording |   | √ | √ | √ |  |  |   |

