### **7.1. Criteria for AE assessment**

Common AEs will include:

(1) LOPM-related: Worsening low back pain, restricted lumbar mobility, aggravated lower limb numbness or pain.

(2) Drug-related: Gastrointestinal reactions (e.g., constipation, epigastric pain, nausea, vomiting), allergic reactions (e.g., skin rash, urticaria), and other side effects such as physical dependence or drug tolerance.

SAEs will be defined as progressively worsening symptoms, including:

- (1) Muscle weakness.
- (2) Cauda equina syndrome.
- (3) Severe intractable pain.

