### **7.3. Documentation of Common AEs**

All AEs will be recorded following each treatment session. Particular attention will be given to:

- (1) LOPM-related AEs (e.g., symptom exacerbation).
- (2) Drug-related AEs (e.g., gastrointestinal disturbances, cutaneous allergic reactions).
- (3) Other potential treatment-emergent AEs, which will be actively solicited and documented.

For each AE, the following details will be collected:

- (1) Clinical manifestations.
- (2) Severity (mild/moderate/severe).
- (3) Onset date.
- (4) Duration.
- (5) Resolution date.
- (6) Interventions applied.
- (7) Assessed causality to treatment (definite/probable/possible/unlikely/unrelated);
- (8) Outcome.

A comprehensive analysis will be performed, accounting for comorbidities and concomitant therapies, to evaluate their association with the study treatment. These data will be used to systematically characterize:

- (1) Complications.
- (2) Contraindications.
- (3) Indications.

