### **7.4. Management of AEs**

- (1) LOPM-related AEs

A small subset of patients may experience worsening lumbar symptoms or reduced mobility during LOPM, typically due to excessive force or abrupt manipulation irritating nerve roots. Recommended management will include:

- 1) Immediate rest in a supine position until symptom relief.
  - 2) Lumbar brace support during ambulation post-recovery.
  - 3) Analgesics (oral or intravenous) if symptoms persist, with resolution typically within 24 – 48 hours.
- (2) Drug-related AEs:

Gastrointestinal reactions (e.g., epigastric pain, nausea, constipation, vomiting), allergic reactions, or dependence/tolerance may occur. Management follows:

- 1) Reassessment of drug continuation based on causality.
  - 2) Discontinuation if warranted, with documented follow-up to monitor outcomes.
- (3) SAEs

For progressive symptoms (e.g., muscle weakness, cauda equina syndrome, or intractable pain):

- 1) Immediate clinical evaluation by a physician will be conducted.
- 2) Surgical intervention if clinically indicated will be conducted.
- (4) Protocol for AE Reporting

All AEs will require:

- 1) Prompt protective measures by investigators.
- 2) Notification of the IRB and lead research unit within 24 hours.
- 3) Signed, dated reports submitted per regulatory standards.

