#### **11.3.3 Risk mitigation strategies**

- (1) Pre-screening: Exclusion of high-risk participants (e.g., spinal instability).
- (2) Real-time monitoring: Protocol-defined thresholds for therapy discontinuation.
- (3) SAE protocols: Immediate surgical referral for neurological deficits.

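### Scheduled adverse event recording ends at Week 2 of 26, and the Week 26 disc resorption rule makes no exception for a herniation that was operated on

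*Protocol*

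**What the plan says.** **Adverse event schedule.** In the study schedule, the row "Adverse events recording" is ticked at Day 3, Week 1 and Week 2 and is blank at Weeks 6, 14 and 26. The Summary and sections 6.1 and 6.2 likewise place adverse event collection at 2 weeks. Section 7.3 adds: "All AEs will be recorded following each treatment session". Treatment lasts 2 weeks and is followed by 24 weeks of follow-up (Summary).

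**Serious events and surgery.** Section 7.1 states: "SAEs will be defined as progressively worsening symptoms, including" muscle weakness, cauda equina syndrome and severe intractable pain. For these events section 7.4 states: "Surgical intervention if clinically indicated will be conducted". Section 11.3.3 promises: "Immediate surgical referral for neurological deficits".

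**Follow-up after stopping.** Section 4.5 says: "All discontinued participants will be followed as per protocol". Section 4.4 says: "All data from withdrawn participants will be included in the final intention-to-treat (ITT) analysis to maintain data integrity".

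**Disc resorption.** Under section 6.3, a reduction of at least 40% in sagittal herniation area between baseline and Week 26 is "defined as the occurrence of disc resorption. The disc resorption rates will be calculated". Resorption rate and adverse events are both listed as secondary outcomes (6.1). Section 10.6 compares categorical outcomes between arms by chi-square or Fisher's exact test.

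**The concern.** The events that section 7.1 calls serious are progressive, so they need not appear within the 14 days of treatment. Scheduled questions about them stop there, even though three further visits take place in every arm. Comparing the arms on these events would then rest on 2 weeks of systematic recording plus whatever is reported spontaneously afterwards.

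The same gap touches the MRI outcome. The protocol sends a patient with neurological worsening to surgery when indicated. Surgery on the disc can reduce the herniation area, and 6.3 decides resorption on area alone. A treatment failure followed by an operation could then be scored as a success. The error runs in the wrong direction: an arm with more operations would tend to show a better resorption rate. Since no visit asks about surgery, nothing in the scheduled data would reliably identify these patients at analysis.

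**Working it through.** **1. What is scheduled after Week 2**

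| Visit | ODI, leg and back VAS, SF-12 | Adverse events | MRI |
|---|---|---|---|
| Day 3, Week 1, Week 2 | yes | yes | no |
| Weeks 6, 14 | yes | no | no |
| Week 26 | yes | no | yes |

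Adverse events are scheduled at 3 of 6 post-baseline visits. Weeks without scheduled recording: 26 − 2 = 24, and 24/26 = 92%. The blank cells are not an accident of table extraction, because the Summary, 6.1 and 6.2 also give 2 weeks. Recording tied to treatment sessions (7.3) ends with treatment.

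**2. What can still capture a late event**
- Serious event reporting within 24 hours (5.6) and notification of all adverse events within 24 hours (7.4). Neither has an end date, but both need the event to come to notice.
- Safety monitoring of discontinued participants until unresolved events settle (4.5). This covers events already known.
- ODI and VAS at Weeks 6, 14 and 26. These measure pain and disability, but not muscle weakness, cauda equina syndrome or an operation.

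**3. The path of an operated patient**
- Spinal surgery excludes a patient at entry only (4.3). It is not listed as a reason for discontinuation (4.5).
- If the patient is discontinued, 4.5 continues follow-up, which includes the Week 26 MRI.
- If the MRI is done and the area has fallen by at least 40%, 6.3 counts the patient as resorbed.
- Section 10.6 states no rule for surgery.

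**4. Size**

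The protocol gives no figure for this point, only the sample size. The target of 146 per arm is internally consistent: 3 × 146 = 438, and the site table gives 42 + 12 × 33 = 438.

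Shift in an arm's rate for one patient counted as resorbed instead of not resorbed: 1/146 = 0.68 points. If the stated 15% dropout leaves 146 × 0.85 = 124 analysed, it is 1/124 = 0.81 points.

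Anything further needs assumptions. Let s be the share operated on before Week 26 and r the resorption rate without surgery. Assume every operated herniation shrinks by at least 40%.
- Rate as written: s + (1 − s)r.
- Rate if operated patients count as not resorbed: (1 − s)r. The difference is s.
- Excess over r itself: s(1 − r).

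| s (assumed) | Patients per arm, about | Excess over r, for r = 40% to 20% (assumed) |
|---|---|---|
| 2% | 3 | 1.2 to 1.6 points |
| 5% | 7 | 3.0 to 4.0 points |
| 10% | 15 | 6.0 to 8.0 points |

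Only an imbalance between arms biases the comparison. Take an assumed excess of 5 operated patients in one arm: 5/146 = 3.4 points. The standard error of a difference in rates is √(2r(1 − r)/146), which is 4.7 points at r = 20% and 5.9 points at r = 50%. The shift is therefore 3.42/5.85 = 0.58 to 3.42/4.68 = 0.73 standard errors.

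**The case against.** Several points on the other side stand.

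- **A reader might infer that later worsening goes unrecorded.** The documents do not support that. ODI and both VAS scales are scored at Weeks 6, 14 and 26 in all arms, so severe pain, one of the three events named in 7.1, would show on a scheduled scale. The gap is in new adverse events, neurological status and surgery.
- **A reader might infer that late serious events are lost.** That does not follow either. The 24-hour reporting in 5.6 and 7.4 has no end date. Adverse event reporting is audited (8.3, 8.5), and ethics committees review serious events (11.2, 11.7). Cauda equina syndrome leading to surgery is likely to come to notice. What remains is that such capture is spontaneous, and it is less certain for milder deficit or for an operation done elsewhere.
- **The operated patient may never reach the MRI.** Section 4.4 lets investigators withdraw a patient for deteriorating health and asks for a final assessment only where possible. Keeping existing data in the ITT analysis does not create a scan. Section 4.5 points the other way, so misclassification is possible under the rules but not certain.
- **Two spine surgeons measure the images and would probably notice an operated disc.** Section 6.3 gives them no instruction for that case, and area decides the outcome.
- **Handling of surgery could be left to the statistical analysis plan.** A plan that is not shown may well reclassify these patients. It cannot supply surgery dates or neurological events that no visit collects, and the protocol itself fixes both the schedule and the resorption definition.

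**Conclusion.** The point holds in limited form. After Week 2, no scheduled visit asks about new adverse events, neurological deficit or spinal surgery. As 6.3 is written, an operated patient who stays in follow-up, has the Week 26 MRI and shows the required area reduction counts as resorbed.

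The size cannot be derived from the protocol. Each such patient moves an arm's rate by at most about 0.7 points with 146 in the denominator, or about 0.8 with 124. It would be tempting to conclude that the resorption comparison is biased by several points. The documents do not support that: they give no surgery rate and no resorption rate, section 11.3.2 calls severe events rare, and sections 4.2 and 4.3 restrict entry to moderate pain and exclude marked weakness, cauda equina injury and persistent deficit with surgical indications. The 2% to 10% range above is purely illustrative. If surgery is rare and balanced, the effect is probably small.

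The primary outcome is untouched. The change is still worth making because it is cheap, closes a gap in safety capture whatever the surgery rate, and removes a misclassification that would favour the arm with more operations.

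**What to change.** 1. In the study schedule, tick adverse event and serious adverse event recording at Weeks 6, 14 and 26 in all three arms, and bring 6.1, 6.2 and the Summary into line.
2. Add one case report form item at those visits: new neurological deficit (leg weakness, cauda equina symptoms), and any spinal surgery or invasive disc procedure, each yes or no with date.
3. In 6.3, state that a herniation operated on before the Week 26 MRI is not counted as resorption, and report the number operated on by arm.

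**Cost.** One form item at three visits that already take place and one clause in the definition; no new visit, scan or participant. Some unrelated adverse events will be recorded during follow-up, and the reported resorption rate may be slightly lower.
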